## Methods and analysis

### Study design

The trial is a multicenter, prospective, double-blind crossover randomized controlled trial (RCT). The overall process is in Figure 2. In this study, we will include 62 moderate to severe post-stroke hemiplegia patients who had stable disease after 1 year of conservative treatment in multiple neuro medical centers in the General Hospital of the People’s Liberation Army of China et al. All patients included in the study will undergo deep brain electrode implantation. They will be randomly postoperatively divided into a DBS group and a control group, with 31 patients in each group. 1 month after surgery, the DBS group will be given electrical stimulation treatment, while the control group will undergo routine observation. Following up in the 3rd and 6th months after surgery. After the follow-up, all patients will stop electrical stimulation treatment for 2 weeks. After the 2-week washout period, the control group will start electrical stimulation treatment, and the DBS group will continue observation. Outpatient follow-up in the 6th and 9th months after surgery. After the follow-up, all patients will undergo electrical stimulation treatment. Observe for a long time. The leading outcome measure of follow-up is the pre-and post-change score on the Fugl-Meyer Assessment Upper Extremity Scale (FMA-UE). In addition, we will follow up on changes in the secondary outcomes of balance function, neuropsychiatric behavior, Post-stroke Spasticity, fall risk, activities of daily living, and quality of life.

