#### Randomization

The 62 patients will be enrolled in the group undergoing deep brain electrode implantation. The 62 patients will be randomly divided into two groups at a ratio of 1:1 using a simple random grouping method, with 31 patients in the DBS group and the control group. First, random numbers will be automatically generated by the OpenClinica clinical trial data management platform to achieve centralized randomization. When a new patient meets the inclusion and exclusion criteria and signs the informed consent form, each research center can apply for the patient’s randomization number after filling in the patient’s basic information in OpenClinica. The random numbers will be automatically issued by the system, and only one coordinator in each center has access. All patients included in the study will receive DBS implantation after baseline assessment and were then randomly divided into two groups in a 1:1 ratio: DBS treatment group and control group. The former will start electrical stimulation treatment 1 month after the operation. Specialists will assess the patient’s recovery status through the remote rehabilitation system every week and guide rehabilitation training and electrical stimulation treatment. The latter will receive the same rehabilitation training under the face-to-face guidance of experts, except for the power-on (sham stimulation, the power-on stimulation parameter was 0). Experts will evaluate the patient’s recovery and adjust rehabilitation strategies every week in the outpatient clinic. The study is blinded to participants, scale raters, and data analysts. Allocation information will be kept in opaque, sealed envelopes by a designated person not involved in the study, thus ensuring the concealment of random assignment.

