#### Blind method

To ensure study quality, all operators, therapists, patients, evaluators, and analysts will remain blinded to assignments and interventions until data collection, analysis, and video recording are completed. During video recording, patients wear surgical caps to conceal the data collection time point. These videos will be uploaded to a central unit and scored by two neurologists, without knowledge of whether the patient is receiving DBS treatment. The data administrator will label the groups as A and B for analysis. However, to safeguard patient safety, the operating doctor cannot be blinded to provide timely treatment in case of emergency. Overall, patient safety is our utmost priority (44).

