## Data management and analysis

### Data management

Before the study begins, all researchers receive comprehensive training on the protocol so that subjects have a clear understanding of the testing requirements subjects can better cooperate and provide more realistic information during the testing process. During the follow-up period, oral medications can be needed, but medications that may significantly interfere with the study results are prohibited from being used as auxiliary treatment. All medications should stopped 24 h before each follow-up assessment. If discomfort during the period, a remote program control should be carried out in time to adjust the stimulation parameters. The follow-up method is mainly outpatient follow-up. When irresistible factors occur, telephone contact and WeChat video connection can be temporarily used instead. However, during subsequent outpatient visits, all information obtained from the last non-outpatient visit must be shared with the patient. Check with your family members to ensure the authenticity and accuracy of the information. All researchers will use unified, standardized, normative, and internationally accepted assessment scales and case report forms (CRF). Before surgery, perioperatively, and 1 month, 3 months, 6 months, 9 months, and 12 months after surgery, blinded professional evaluators strictly followed the standardized evaluation scale and evaluation process to conduct evaluations and record standardized videos. Professional clinicians not related to this study will re-evaluate the scores at each follow-up time point and compare the scores obtained with the first score. If the difference is not significant, the first evaluation results will used. If the difference is too big, a third evaluation will performed. Once the assessment results are accurate, the recorder uploads the data to the case report form. During the data collection process, two data supervisors will review the contents of CRF to ensure the authenticity and accuracy of the data. If there are data errors or incomplete information, the data manager sends it back to the appropriate center, where the researcher checks the original file, rechecks, and updates the data. At the end of the trial, the data administrator will lock the database and send the data separately to two data analysts for analysis. During the research process, to ensure the quality and accuracy of the data, only designated personnel not related to this study can view and modify the data, and each modification will be recorded, and personnel related to this trial will remain evasive throughout the process.

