
### Data analysis

All data analysis will based on IBM SPSS Statistics 25.0, describing the total score of each scale at each follow-up and the change from baseline at each visit after treatment. Measurement data using mean ± standard deviation to describe. Count data Use numerical values (%) to describe, and use group t-test or Wilcoxon to compare between groups according to the characteristics of the data. Intra-group comparisons were performed using rank sum-test, paired t-test or paired signed rank-test. For comparisons of pre-and post-treatment change values based on baseline general information, appropriate multivariate analysis models were used to correct for the effects of confounding factors or covariates based on the data situation. The single-item count data of each scale used the chi-square test or the exact probability test, and the grade data used the Wilcoxon rank sum test. A paired rank sum test and repeated measures analysis of variance were used to analyze the changes in score data within the group before and after treatment. The effectiveness measurement index is the improvement rate of each clinical scale at different follow-up times = (scale score at each postoperative time point − preoperative score) / preoperative score * 100%. A score improvement rate > 25% is considered effective. Safety observation indicators are all postoperative adverse reactions, including surgery-related adverse reactions, device-related adverse reactions, and stimulation-related adverse reactions. The type, number of cases, occurrence time, treatment measures, and prognosis of adverse events are recorded. The incidence of adverse events is defined as the number of patients in which it occurs divided by the number of all patients, and an adverse event rate of less than 5% is considered safe.

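### Weekly rehabilitation guidance is described as remote for the DBS group and face to face for the sham group, so first-period differences may mix stimulation with contact mode

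*Protocol article*

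**What the plan says.** All the text is in the protocol article.

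- **Randomization, DBS group.** Once stimulation starts, 1 month after surgery, specialists assess recovery "through the remote rehabilitation system every week and guide rehabilitation training and electrical stimulation treatment".
- **Randomization, control group.** "The latter will receive the same rehabilitation training under the face-to-face guidance of experts, except for the power-on"; sham is defined as powered on with the stimulation parameter at 0. The next sentence has experts evaluate the patient's "recovery and adjust rehabilitation strategies every week in the outpatient clinic".
- **Blind method.** "all operators, therapists, patients, evaluators, and analysts will remain blinded to assignments and interventions" until data collection, analysis and video recording are complete. The doctor who operates is then excepted for safety reasons.
- **Figure 3 caption.** Stimulation is shown in an in-clinic rehabilitation session, where a therapist triggers each pulse by push button.
- **Study design.** At crossover, after the 2-week washout, "the control group will start electrical stimulation treatment, and the DBS group will continue observation". Contact mode is not mentioned.
- **Data analysis.** The plan is to "use group t-test or Wilcoxon to compare between groups according to the characteristics of the data", and to describe "the change from baseline at each visit after treatment".
- **Data management.** "The follow-up method is mainly outpatient follow-up". This concerns assessment visits, not the weekly guidance. The same section provides for remote adjustment of stimulation parameters if a patient has discomfort.

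**The concern.** The Randomization section presents power-on as the only difference in care between the groups, yet it also describes different ways of delivering the weekly guidance. Rehabilitation contact could plausibly affect FMA-UE, the primary outcome. A difference at month 3 or month 6 could then come from stimulation, from contact mode, or from both, and a reader could not tell which.

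There is also a blinding issue. The therapist giving the guidance knows whether a session is remote or in person, and guidance of stimulation is described only alongside the remote sessions. Blinded video scoring protects the ratings. It does not protect what therapists and patients do between visits, or self-reported outcomes such as the SF-36.

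**Working it through.** The article gives no figure for the effect of contact mode, so the main check is to set the texts side by side.

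**Step 1: can the text be read so that the arms are equal?**

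- Plain reading: the former and latter groups are introduced in turn, and each is followed by its own weekly arrangement. DBS is remote; sham is face to face and in clinic.
- If the remote sentence covers both groups, the sham group still has face-to-face guidance on top.
- If the outpatient sentence covers both groups, face-to-face training guidance is still stated only for the sham group.
- If the Figure 3 caption describes actual delivery, DBS patients also meet a therapist in clinic. The arms may then be closer, but the caption conflicts with remotely guided stimulation and says nothing about sham sessions.

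No reading of the Randomization section by itself removes the difference. The caption makes its extent uncertain.

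**Step 2: what would each comparison estimate on the plain reading?** Let t be the stimulation effect and d the gain from face-to-face over remote contact. Assume no carry-over and the same t and d in both periods. Differences are stimulated minus sham.

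- Months 1 to 6: stimulated patients are remote and sham patients face to face, giving t − d.
- Second period, contact mode stays with the group: the stimulated patients are now the face-to-face ones, giving t + d. The mean over periods is [(t − d) + (t + d)]/2 = t.
- Second period, contact mode follows stimulation: t − d again, and the mean over periods is t − d.

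Any effect of guessed allocation would come on top and could run in favour of DBS. The net sign is therefore not fixed even if d is positive.

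**Step 3: illustration of scale, on assumed values only.** Suppose t = 0 and contact mode shifts the group difference by b points in either direction. With 31 per group, SE = SD × √(2/31), and the chance of a two-sided 5% result is Φ(b/SE − 1.96) + Φ(−b/SE − 1.96). The SDs 6.30 and 12.23 are those in the Sample size section, and 9.73 = √[(6.30² + 12.23²)/2]. They are SDs of scores, not of change, and the values of b are assumptions.

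| SD | b = 1 | b = 2 | b = 3 | b = 4 |
|---|---|---|---|---|
| 6.30 | 9.6% | 23.9% | 46.6% | 70.5% |
| 9.73 | 6.9% | 12.8% | 22.9% | 36.7% |
| 12.23 | 6.2% | 9.9% | 16.2% | 25.1% |

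Example: SD 6.30 and b = 4 give SE = 6.30 × √(2/31) = 1.60, b/SE = 2.50, and Φ(0.54) = 0.705. The table shows only that a shift of a few points would matter at this sample size. It is not evidence that such a shift exists.

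**The case against.** The best case on the other side has four parts.

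1. **Intent and the caption.** The section says the training is the same, the two weekly sentences name no group, and Figure 3 puts DBS patients in the clinic. A reader might infer that all 31 DBS patients are remote and all 31 controls in clinic, so that contact mode and arm coincide completely. The article does not establish that. Coding contact mode as identical to arm merely restates one reading. What stands is that the text, followed as written, treats the arms differently, and that the article disagrees with itself about where stimulation is delivered.
2. **Patient blinding.** A reader might infer that contact mode unblinds patients. Patients see only their own mode, and nothing says they are told which mode belongs to which arm. This objection holds. The cue is mainly to therapists, and even for them it depends on knowing the mapping or serving both arms. The shortcomings in the Discussion already concede a larger cue, that active stimulation is likely to be noticed.
3. **Crossover.** If contact mode stays with the group, it cancels from a two-period estimate. That is correct. A condensed article may leave contact mode after crossover to the full protocol, so its silence is not an error in itself. The month 3 and month 6 comparisons remain exposed on the plain reading.
4. **Direction.** Bias against DBS is one possibility, if in-person contact helps. Guessed allocation could favour DBS. No direction can be claimed.

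**Conclusion.** The concern holds in limited form. As written, the Randomization section gives the two groups different weekly contact modes. This contradicts its own statement that only power-on differs, sits badly with therapist blinding, and conflicts with the in-clinic delivery in the Figure 3 caption.

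If the text is followed, first-period FMA-UE differences estimate t − d rather than t, with d unknown in size and the net bias unknown in direction. Whether a two-period estimate is affected depends on what happens to contact mode at crossover. The documents do not support calling the trial unblinded to patients, treating the confounding as proven and complete, or saying that the crossover result is compromised. This should be fixed, because the contradiction is plain in the text even though its effect cannot be sized.

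**What to change.** In the Randomization section, specify one contact mode, weekly schedule, equipment set and programming procedure for both groups in both periods, with output at 0 during sham, and state that none of these changes at crossover. Make that section and the Figure 3 caption agree on where and how stimulation is delivered. This has to be settled first, since remote contact for everyone does not fit push-button delivery in the clinic.

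**Cost.** No extra patients. From month 1 to month 6 there are about 5 × 52/12 = 21.7 weekly contacts per patient. Remote contact for all would therefore remove about 22 clinic visits per control patient; face-to-face contact for all would add about 22 per DBS patient.

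The Discussion says the study is already under way. If practice is already equal, a correction of wording is enough. If the section describes actual practice, the change is an amendment to delivery in a running trial. Patients already treated under the old arrangement should then be identified and a sensitivity analysis by contact mode reported. Among patients treated only under the old arrangement, no covariate adjustment could separate contact mode from stimulation in the first period if the two coincided. The analysis would have to draw on patients treated after the change.

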#### Blind method

To ensure study quality, all operators, therapists, patients, evaluators, and analysts will remain blinded to assignments and interventions until data collection, analysis, and video recording are completed. During video recording, patients wear surgical caps to conceal the data collection time point. These videos will be uploaded to a central unit and scored by two neurologists, without knowledge of whether the patient is receiving DBS treatment. The data administrator will label the groups as A and B for analysis. However, to safeguard patient safety, the operating doctor cannot be blinded to provide timely treatment in case of emergency. Overall, patient safety is our utmost priority (44).

#### Outcome measurements

All outcome measures will be evaluated by professional research assistants 1 week before surgery, during the perioperative period, and at one-month, three-month, six-month, nine-month, and 12-month intervals postoperatively (Table 2). All measurement results will be securely uploaded to a third-party online data management system. The primary outcome measure is the improvement in patients’ motor function before and after deep brain stimulation, assessed primarily through changes in the Fugl-Meyer Assessment Upper Extremity Scale (FMA-UE). Secondary indicators include the evaluation of patients’ balance function, neuropsychiatric behavior, fall risk, activities of daily living (ADL), and quality of life before, after, and at various time points following treatment, along with the calculation of the stroke improvement rate.

**Table 2 tab2:** Participant timeline of data collection.

Study period	Screening	Perioperative period		Follow-up period				
	Enrollment	Allocation/surgery	Postsurgery	1 month	3 month	6 month	9 month	12 month
Number of days	15 ± 7	10 ± 7	3 ± 2	7 ± 3	7 ± 3	7 ± 3	7 ± 3	7 ± 3

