## Discussion

The study is currently being conducted at multiple centers including the Chinese People’s Liberation Army General Hospital. At present, research on the application of DBS in post-stroke motor dysfunction is gradually carried out (66). Slotty et al. (67) used GPi-DBS combined with Vim/ventral nucleus (Vop)-DBS to treat a case of unilateralism secondary to putamen stroke. In studies on patients with dystonia, the results showed that the patient’s motor symptoms were significantly and sustainably improved; Elias et al. included nine studies with a total of 32 patients with post-stroke dyskinesia and found that at least 13 of the patients received DBS treatment (12). Post-motor symptoms improved significantly. Koerbel et al. (68) reported a 48-year-old patient after a thalamic hemorrhagic stroke. After DBS zona incerta (ZI) treatment, the patient’s proximal motor function was significantly improved, the abnormal involuntary movement scale score was significantly reduced. Franzini et al. (15) reported that the motor function of 3 patients with post-stroke motor function deficits improved after DBS treatment of the contralateral internal capsule posterior limb. Baker et al. (7) used cerebellar dentate nucleus-DBS to treat 12 patients with moderate to severe upper limb motor deficits after unilateral stroke. The patients’ upper limb Fugl-Meyuer motor function score increased by 7 points, and the upper limb motor function improved. There was no improvement during the treatment. Serious complications occur. For patients with post-stroke motor dysfunction, the range of stimulation parameters is wide and needs to be adjusted individually according to the stimulation target. Existing literature shows that the optimal stimulation parameters must be determined individually for each patient. The optimal stimulation parameters have not yet been established. The conclusion is still under intense discussion. Paro et al. (12) systematically analyzed 82 DBS electrodes implanted in 53 patients and found that the voltage [M (range)] of 55 leads was 3.4 (2.4~4.0) V, the frequency [M (range)] of 63 leads is 145 (130~185) Hz, and the pulse width [M (range)] is 90 (60~120) μs. However, there are also studies showing that wider pulses (>400 μs) appear to be more effective in enhancing movement and more convenient than shorter pulse widths, and preliminary results from local field potential (LFP) measurements and behavioral tests suggest that lower stimulation frequencies (8–20 Hz) are more appropriate, therefore, we first stimulated with 20 Hz, 400 μs, 2.0–4.5 V pulse width, increasing voltage, and then adjusted the frequency and pulse width according to individual intraoperative behavioral responses. Although a large number of relevant studies have been carried out to initially confirm the unique advantages, effectiveness, and safety of DBS in patients with post-stroke hemiplegia, they are still at the stage of basic animal experiments, case reports and case series reports and large-sample RCTs have not yet been carried out. Research to confirm its effectiveness and safety. Based on this, we designed this research protocol. To our knowledge, this trial protocol is the first to explore the effect of MLR-DBS on improving motor function in stroke survivors. It is also the first RCT in the field of application of DBS in post-stroke motor dysfunction. Research proposal. This multicenter, prospective, randomized, double-blind crossover controlled clinical research protocol is the first to develop and execute a study on the safety, feasibility, and safety of deep brain stimulation (DBS) in the midbrain motor region (MLR) to improve motor dysfunction after stroke plan. The evaluation results were evaluated by random shuffling, and the first evaluation was blindly evaluated with standardized videos for comparison before and after to reduce potential bias. The randomization process of this study was carried out after the surgery of all patients, thus avoiding to a large extent the interference on the study results caused by the surgeon’s inability to implement blinding. Our research team has performed thousands of deep brain electrode implantation surgeries to treat Parkinson’s disease, dystonia, Major syndrome, and other diseases, and has rich clinical and surgical experience. The main purpose of this trial protocol is to improve wheelchair, subacute, and chronic stroke motor dysfunction through MLR-DBS and to study the clinical feasibility and efficacy of MLR-DBS in humans. Study results will demonstrate the effectiveness, efficacy, and safety of MLR-DBS in improving motor function in stroke survivors. Our goal is to maximize the long-term restoration of lost motor function in patients with severe movement disorders. This research program will guide on the importance of integrating existing and different rehabilitation techniques and designing more effective rehabilitation programs. The results of this trial will help to understand the neural mechanisms of MLR-DBS in stroke patients who develop hemiparesis after stroke. Provide clinical evidence support for the large-scale clinical application of DBS technology.

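### The improvement rate and its 25% rule are measured from the preoperative score, not from a score before switch-on, and no FMA-UE is scheduled at the end of the washout

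*Protocol article*

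**What the plan says.** - **Assessment times.** Outcome measurements schedules all outcomes "1 week before surgery, during the perioperative period, and at one-month, three-month, six-month, nine-month, and 12-month intervals postoperatively". Data management repeats the list: "Before surgery, perioperatively, and 1 month, 3 months, 6 months, 9 months, and 12 months after surgery". The FMA row of Table 2 agrees.
- **Start of period 1.** Study design: "1 month after surgery, the DBS group will be given electrical stimulation treatment, while the control group will undergo routine observation". Table 2 marks the DBS group in the month-1 column, where an FMA is also due, without giving the order within the visit.
- **Switch.** Study design: "After the follow-up, all patients will stop electrical stimulation treatment for 2 weeks", and then "After the 2-week washout period, the control group will start electrical stimulation treatment, and the DBS group will continue observation".
- **Reference for change.** Data analysis defines the improvement rate of each scale as "scale score at each postoperative time point − preoperative score) / preoperative score * 100" per cent and calls a rate above 25% effective. It also describes change from baseline and plans paired tests within groups. Randomization places the baseline assessment before implantation.
- **Primary outcome.** Outcome measurements defines it as the improvement in motor function from before to after stimulation, measured by FMA-UE.

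**The concern.** The primary outcome is framed around stimulation, but the reference score predates the operation. Electrode insertion, the postoperative course and any rehabilitation in the first month lie between that score and switch-on. A patient can therefore move towards, or away from, the 25% threshold before receiving any stimulation. The rule is a stated criterion of effectiveness, so a high proportion of patients meeting it could be read as a stimulation effect when part of it is not.

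The second issue is the switch. A crossover relies on the washout, and here nothing is measured when it ends. If the DBS-first arm enters its sham period with residual benefit, no planned score shows this at that moment. An analysis plan cannot recover a score that was never taken.

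**Working it through.** The protocol gives no figure for either issue, and its sample size plays no part in them.

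**1. Size of the reference problem in the 25% rule**

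Inputs: literature pre-treatment mean of 21.92 (Sample size); 25% threshold (Data analysis). Assumed, because the protocol gives no value: a change g of 2 to 4 points between surgery and month 1, and an alternative preoperative score of 40.

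- Score 21.92: threshold 0.25 × 21.92 = 5.48 points. Share supplied before stimulation: 2/5.48 = 36% to 4/5.48 = 73%. Left for stimulation: 5.48 − 2 = 3.48 down to 5.48 − 4 = 1.48 points.
- Score 40: threshold 0.25 × 40 = 10 points. Share: 2/10 = 20% to 4/10 = 40%.
- The sign could be reversed. If surgery cost 2 points, 5.48 + 2 = 7.48 points would be needed from month 1.

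Under the present rule, a patient at 21.92 must exceed 21.92 + 5.48 = 27.40. With month 1 as reference, the bar is 1.25 × 23.92 = 29.90 for g = 2 and 1.25 × 25.92 = 32.40 for g = 4.

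**2. Within-group before/after change**

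The change from the preoperative score is Δ + g while stimulated and g while not, before any time trend. With Δ = 7 (the literature improvement in Sample size) and g = 2 to 4, the stimulated arm would show 9 to 11 points and the sham arm 2 to 4 points with no stimulation at all.

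**3. Contrasts between conditions**

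- Within a patient: (on − pre) − (off − pre) = on − off. The preoperative score cancels. In the percentage form, it remains only as a common divisor.
- Between arms: all patients are implanted and both arms are to have the same rehabilitation, so g is balanced in expectation by randomisation.

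**4. Assessments around the switch, on the Table 2 timeline**

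- Last score before the washout: month 6. Washout ends at about month 6.5. Next score: month 9, about 9 − 6.5 = 2.5 months into period 2.
- Scores between the end of washout and the start of period 2: none.
- Study design instead gives period-2 follow-up as months 6 and 9, which lists month 6 on both sides of the washout. The Abstract and Table 2 point to months 9 and 12. Neither timetable places a visit at the end of washout.

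**5. Should an end-of-washout score be subtracted as a period-2 baseline?**

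Assume Δ = 7, half of it (3.5) still present at the switch and gone by month 9, and no time trend.

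- DBS-first arm: 7 − (0 − 3.5) = 10.5. Control-first arm: 7. Mean (10.5 + 7)/2 = 8.75.
- With the common reference: 7 in each arm, mean 7, which is correct.

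Subtracting the new score could therefore introduce bias. It is useful only as a check.

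**The case against.** A reader might infer that neither stimulation period has a pre-stimulation score. The documents do not support this. The DBS-first arm has an FMA due at month 1, when its stimulation begins. The control arm receives only sham, with the parameter at zero, up to month 6, so its month-6 score is an unstimulated score about two weeks before its own switch-on. The mark in the month-1 column of Table 2 does not show that scoring follows switch-on; the order is simply not stated.

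A reader might also infer that the preoperative reference biases the treatment effect. It does not, as step 3 shows. The hypothesis in Sample size is a between-group one, and the 25% rule applies to both arms alike, so a between-arm comparison of proportions remains a valid randomised comparison. What is distorted is the proportion within each arm, read as a stimulation effect.

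A third inference is that the missing visit shrinks the crossover estimate by a known amount. If a fraction c of the effect carries over, the estimate is Δ(1 − c/2): for Δ = 7 and assumed c of 0.25, 0.5 and 0.75, this gives 6.1, 5.3 and 4.4. But c there is the carryover present when period-2 outcomes are scored, not at month 6.5, and an end-of-washout score would not supply it. The DBS-first arm is scored off stimulation in period 2, the control arm's change from month 6 shows its response free of DBS carryover (though mixed with any time trend), and the period-1 comparison is free of carryover. Nor does the Discussion predict persistence after switch-off: "Our goal is to maximize the long-term restoration of lost motor function" states a treatment goal.

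Finally, patients are stable at one year or more after stroke, so a gain of 2 to 4 points in the month after surgery has no support in the protocol. That is fair, and the range is only an illustration. The choice of reference is still wrong for the stated purpose whatever the size of g.

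**Conclusion.** The point holds in two limited parts.

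- The improvement rate, its 25% rule and the within-group before/after tests attribute to stimulation everything that happens from before surgery to switch-on. On assumed changes of 2 to 4 points, this is 36% to 73% of the threshold at a preoperative score of 21.92 and 20% to 40% at 40. The true size and sign are unknown. The randomised between-arm and on-minus-off contrasts are unaffected.
- No FMA-UE is taken between the end of washout and the start of period 2, so the DBS-first arm's return to its pre-stimulation level is not directly observed. This is a missing check; it does not show that carryover exists or that the crossover estimate is wrong.

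The first part is worth correcting because it affects a stated criterion of effectiveness. The second is a modest improvement to the design.

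**What to change.** 1. State that the month-1 FMA-UE is taken before switch-on in both arms. Use it, in place of the preoperative score, as the reference for change and for the 25% rule. Keep the preoperative score to describe the effect of implantation. This is free, as the score is already collected.
2. Add one FMA-UE to Table 2 at the end of washout, in both arms, before devices are reset. Report the DBS-first arm's end-of-washout minus month-1 difference against the same difference in the control arm, as a check on the washout only. Do not subtract it as a period-2 baseline in the crossover contrast. The cost is one extra video-scored assessment per patient, with the repeat rating and the 24-hour medication stop that Data management attaches to each follow-up assessment. It may need a visit of its own, because stimulation parameters can be adjusted remotely.
3. Reconcile the period-2 follow-up months in Study design (6 and 9) with the Abstract and Table 2 (9 and 12). This is a text change.
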